#### Surgical phase

Occult metastatic rate of contralateral nodes (positive SNB).

### Participant timeline

A participant timeline and assessments conducted during the trial for the imaging and surgical phases are detailed in tables1^3^.

**Table 1 T1:** Trial assessments performed for the imaging phase (stage 1) main group

Assessments	Screening	Baseline	Examination day	Examination day+24 hours
All stage 1 patients (n=75)				
Inclusion and exclusion criteria	x			
Consent	x			
Registration		x		
Demographic data		x		
Medical history		x		
Concomitant medications		x		
Tumour characteristics		x		
Examination under anaesthesia (standard of care)			x	
Injection of radiotracer and fhSPECT scanning			x	
Sentinel node imaging by SPECT/CT up to 24 hours postinjection				x
AE reporting			x	x

AE, adverse event; fhSPECT, free-hand single photon emission CT.

**Table 2 T2:** Trial assessments performed for the imaging phase (stage 1) subgroup

Assessments	Screening	Baseline	Examination day	Examination day+24 hours	Examination day+4–10 days
Stage 1 subgroup (n=20)					
Inclusion and exclusion criteria	As per stage 1 main group				
Consent					
Registration					
Demographic data					
Medical history					
Concomitant medications					
Tumour characteristics					
Examination under anaesthesia (standard of care)					
Injection of radiotracer and fhSPECT scanning					
Sentinel node imaging by SPECT/CT up to 24 hours postinjection					
AE reporting					x
Local anaesthesia					x
Intratumoural injection of radiotracer					x
SPECT/CT scan					x
Patient acceptability questionnaire					x

AE, adverse event; fhSPECT, free-hand single photon emission CT.

**Table 3 T3:** Trial assessments performed for the surgical phase (stage 2) main group

Assessments	Screening	Baseline	Scanning day*	Examination day
Stage 2 patients (n=75)				
Inclusion and exclusion criteria	x			
Consent	x			
Registration		x		
Demographic data		x		
Medical history		x		
Concomitant medications		x		
Tumour characteristics		x		
Outpatient radiotracer injection followed by SPECT/CT*			x*	
Examination under anaesthesia (standard of care)				x
Injection of radiotracer and fhSPECT scanning*				x*
Excision of contralateral nodes identified on imaging				x*
AE reporting			x	x

* scanning protocol dependent on outcome of imaging phase

AE, adverse event; fhSPECT, free-hand single photon emission CT.

### Sample size

Extrapolating from oral cancer models, our sample size is pragmatically based on the number of eligible cases seen and minimum cases required to establish a baseline lymphatic pattern.

### Imaging phase

For 75 patients our expected agreement is 96%, with an exact 95% CI width of approximately 10%. In addition, we will have 80% power to demonstrate that the agreement exceeds 88% using a one-sided test at a 5% significance level.

### Surgical phase

75 patients will be considered for SNB. Of these, 20%–30% (15–23 patients) are expected to have sentinel nodes on the opposite side of the neck. An exact 95% CI for this proportion is expected to have precision of ±11%.

### Recruitment

Patients diagnosed with OPC who fulfil the inclusion/exclusion criteria will be identified during H&N MDT meetings and in outpatient clinics. In each stage, up to 75 patients will be recruited over 18 months at five centres.

### Data collection methods

#### Pre-intervention assessments

No trial-specific procedures will be needed to be carried out to assess eligibility. All information required to determine eligibility will be available from the standard medical records and identified as specified above either during the H&N MDT meeting or in the outpatient clinic.

Relevant clinical information will be recorded in the CRFs. Data recorded will include:

Demographics.Relevant medical history.Concomitant medication.Tumour characteristics, including size, type, grade, TNM stage, p16 status.

#### Participant registration

Consented, eligible participants will be registered by completing the trial’s online registration form. A unique pseudo-anonymised subject number will be generated. This number will be used to identify all patient data and tissue samples for the trial.

#### Data collection tools and source document identification

Data will be collected from sites using electronic CRFs (eCRFs). Source data are contained in source documents (medical records, which include laboratory and other clinical reports, case notes and hospital trust computer databases) and will be accurately transcribed onto the eCRF. The delegation log will identify all those personnel with responsibilities for data collection and handling, including those who have access to the trial database.

#### Completing case report forms

Data will be collected by eCRFs and will be verified using manual and electronic validation checks. All eCRFs will be completed by staff that are listed on the site staff delegation log and authorised by the Principal Investigator (PI) to perform this duty. The PI is responsible for the accuracy of all data reported in the eCRF.

#### Imaging phase outcome measure data collection

Each assessor fulfils a CRF per case with three questions:

Are there contralateral nodes on SPECT/CT? No/Yes (record neck level).Are there contralateral nodes on fhSPECT? No/Yes (record neck level).Do the contralateral nodes co-localise? Yes/No.

If contralateral nodes are shown in SPECT/CT but not on fhSPECT, this will be recorded as a false negative result (unless these can be attributed to second echelon nodes) for fhSPECT and vice versa. Contralateral drainage on either modality will be recorded as a true positive result. fhSPECT should achieve sensitivity >94% compared with SPECT/CT.

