**Methods and analysis:**

The design is a prospective multicentre cohort trial to understand the lymphatic drainage pattern in 150 patients with OPC and unilateral neck metastases. The trial has two phases: (1) *imaging phase (n=75)*—aim: develop an imaging protocol to establish the lymphatic drainage pattern in a population of patients with proven unilateral neck metastasis from OPC. The intervention will involve peritumoural injection of radiotracer followed by fhSPECT scan under general anaesthesia (GA) (at time of examination under anaesthetic). A SPECT/CT scan (gold standard for lymphatic mapping) will be carried out subsequently as a comparator. The primary outcome is the rate of contralateral drainage. Secondary outcome is the accuracy of fhSPECT versus SPECT/CT. The number of contralateral nodes on SPECT/CT will be used as the denominator in calculating the sensitivity of fhSPECT in independently verified images. fhSPECT should achieve sensitivity >94%. A minimum number of 20/75 patients will be required to demonstrate contralateral drainage to proceed to the surgical stage. An imaging substudy (n=20) aims to develop a secondary imaging protocol in the event of <94% sensitivity of intraoperative fhSPECT. To investigate the sensitivity of outpatient imaging (single injection of radiotracer and SPECT/CT) compared with gold standard (SPECT/CT from initial imaging phase) and the acceptability of outpatient injection compared with under GA. Twenty patients from the imaging phase with easily accessible tumours will be invited to undergo a second imaging; (2) *Surgical phase (n=75)*—aim: demonstrate the utility of surgically staging the contralateral neck using sentinel node biopsy (SNB). The primary outcome of this surgical phase is the occult metastatic rate of contralateral nodes (positive SNB). The contralateral drainage rate will be identified during the imaging phase, with an expected SNB positive rate of excised nodes ranging from 25% to 40%.

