### Outcomes

#### Imaging phase

Primary outcome:

Rate of contralateral drainage. fhSPECT and SPECT/CT images reviewed by two independent assessors. Sum of non-duplicated contralateral hotspots taken as the true contralateral drainage rate. Minimum of 20/75 patients must demonstrate contralateral drainage to proceed to surgical stage.

Secondary outcome:

Accuracy of fhSPECT compared with SPECT/CT. Number of contralateral nodes on SPECT/CT used as denominator in calculating sensitivity of fhSPECT by independently verified images.

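### As written, the fhSPECT scoring rule makes two non-matching contralateral nodes a true positive and conflicts with the node-based sensitivity definition behind the >94% threshold

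*Protocol article*

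**What the plan says.** All references are to the protocol article.

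- **Imaging phase outcome measure data collection.** The form is completed once per patient: "Each assessor fulfils a CRF per case with three questions". The first two questions ask whether each scan shows contralateral nodes, with neck level. The third is "Do the contralateral nodes co-localise? Yes/No".
- **Scoring, same section.** The false-negative rule is "If contralateral nodes are shown in SPECT/CT but not on fhSPECT, this will be recorded as a false negative result", with an exception for second-echelon nodes. The next sentence is "Contralateral drainage on either modality will be recorded as a true positive result". The threshold follows: "fhSPECT should achieve sensitivity >94% compared with SPECT/CT".
- **Outcomes, Imaging phase** (and the Abstract). The sensitivity denominator is a count of nodes: "Number of contralateral nodes on SPECT/CT used as denominator in calculating sensitivity of fhSPECT by independently verified images". The primary outcome is separate: it sums the non-duplicated contralateral hotspots over both scans.
- **Statistical methods, Validating image protocol.** SPECT/CT is the gold standard. Each pair of scans is also classed as agreeing or disagreeing, without saying whether agreement requires the same node.
- **Use of the threshold.** The Abstract says that the imaging substudy is to "develop a secondary imaging protocol in the event of <94% sensitivity of intraoperative fhSPECT". The Surgical phase section lists the two possible imaging routes and says that the imaging-phase outcomes will inform the choice. Under either route, Table 3 then has "Excision of contralateral nodes identified on imaging".

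**The concern.** The surgical phase acts on particular nodes. On the fhSPECT route, the node that fhSPECT shows determines which tissue is examined for the occult metastatic rate. Validation of fhSPECT should therefore ask whether it found the node that SPECT/CT found, not only whether both scans lit up on the same side of the neck.

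The form collects what is needed to judge this, but the scoring sentences are worded in terms of presence. If the true-positive sentence governs, a scan that often marks a different contralateral node could clear the >94% threshold. SNB would then sample nodes other than those on the reference scan, and the occult metastatic rate could be understated. If the node denominator governs, the same data could fail the threshold and point to the fallback protocol. The choice of reading should be fixed before the data are seen.

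**Working it through.** **1. The plan's own imaging-phase figures.** Sample size, Imaging phase, gives n = 75, expected agreement 96%, null value 88%, one-sided 5%, 80% power and an exact 95% CI width of about 10%.

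- Exact binomial test: the smallest rejection count with level at most 5% is 71/75. The level is P(X ≥ 71 | 75, 0.88) = 0.045 and the power is P(X ≥ 71 | 75, 0.96) = 0.819.
- Clopper-Pearson interval for 72/75 (96%): 88.8% to 99.2%, width 10.4 points.

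These figures reproduce. They concern overall agreement in 75 patients and do not bear on the >94% sensitivity rule.

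**2. The scoring sentences side by side.**

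| SPECT/CT | fhSPECT | Co-localise | Either-modality sentence | False-negative sentence and node denominator |
|---|---|---|---|---|
| Yes | Yes | Yes | True positive | Detected |
| Yes | Yes | No | True positive | SPECT/CT node not shown on fhSPECT: false negative, if read per node |
| Yes | No | – | True positive | False negative |

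The second-echelon exception applies to the last column. The second row is the discordant case: two sentences, two scores. The third row is a direct contradiction. Applied in full, the either-modality sentence leaves no false negatives, so sensitivity would always be 100%.

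**3. Size for the discordant case.** The article gives no mislocalisation rate, so the following are assumptions:

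- m = 20 SPECT/CT-positive patients, one contralateral node each. The number is borrowed from the 20/75 minimum for contralateral drainage.
- fhSPECT shows some contralateral signal in a proportion d = 0.98 of them.
- A proportion w of those signals is at a different node.
- SPECT/CT-only cases count as false negatives, as the false-negative sentence says.

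Passing needs x/20 > 0.94. Since 0.94 × 20 = 18.8, x must be at least 19.

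P(pass) = p^20 + 20 p^19 (1 − p), with p = d if location is ignored and p = d(1 − w) if it must match.

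- Location ignored, any w: p = 0.98, P = 0.94.
- w = 5%: p = 0.98 × 0.95 = 0.931, P = 0.59.
- w = 10%: p = 0.98 × 0.90 = 0.882, P = 0.30.
- w = 20%: p = 0.98 × 0.80 = 0.784, P = 0.05.

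**4. Range over the assumptions.**

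| m (needed to pass) | d | Location ignored | w = 5% | w = 10% | w = 20% |
|---|---|---|---|---|---|
| 15 (15) | 0.98 | 0.74 | 0.34 | 0.15 | 0.03 |
| 20 (19) | 0.96 | 0.81 | 0.46 | 0.22 | 0.04 |
| 20 (19) | 0.98 | 0.94 | 0.59 | 0.30 | 0.05 |
| 20 (19) | 1.00 | 1.00 | 0.74 | 0.39 | 0.07 |
| 23 (22) | 0.98 | 0.92 | 0.52 | 0.23 | 0.03 |
| 30 (29) | 0.98 | 0.88 | 0.38 | 0.12 | 0.01 |

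The levels move with m and d, but the gap between the two readings is large throughout.

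**The case against.** The strongest reply is that the article, read as a whole, does not score by presence alone.

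- The denominator is SPECT/CT nodes. On that definition a missed node is not detected because another lit up.
- The false-negative sentence can be read per node, and its second-echelon exception requires knowing which node is which.
- The either-modality sentence would force 100% sensitivity if applied to fhSPECT, so it was probably meant for the primary drainage rate, which pools both scans.
- Counting non-duplicated hotspots requires matching across scans, and the agree/disagree outcome is another natural use of the third question.
- Mapping a form item to a derived variable is often left to the SAP.

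Much of this stands. A reader might infer that the plan has settled on location-blind scoring, that the co-localisation answer is never used, or that fhSPECT passes at any rate of mislocalisation. The article does not support these as statements of fact; they follow only if the either-modality sentence governs. A reader might also take the >94% threshold as the go/no-go for surgery. The stated minimum for proceeding is 20/75 patients with contralateral drainage; the sensitivity threshold bears on which imaging route is used.

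The reply does not remove the defect. The article does not defer the scoring: it defines false negative, true positive and threshold in one paragraph. The disputed sentence uses accuracy vocabulary and sits between the false-negative rule and the sensitivity threshold. The form is per case, with one co-localisation answer, while the denominator is per node.

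**Conclusion.** The point holds as an internal contradiction with a material consequence. The true-positive sentence, taken literally, counts contralateral nodes that do not match as a success for fhSPECT, contradicts the false-negative sentence before it, and does not fit the node denominator. The same discordant case can score either way against >94%.

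The conflict in wording rests on the text alone. Its size does not: the probabilities in the working depend on assumed detection and mislocalisation rates, one node per patient and independence between patients. They show that the choice of reading can decide the result, not that fhSPECT mislocalises. It should be corrected before the mid-trial decision; the article reports that recruitment is still under way.

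**What to change.** 1. In Imaging phase outcome measure data collection, limit the either-modality sentence to the primary drainage rate defined under Outcomes.
2. For fhSPECT accuracy, name the SPECT/CT contralateral node as the unit. Count it as a true positive only if it co-localises with an fhSPECT node, matched by the recorded neck level; otherwise count it as a false negative.
3. Keep the second-echelon exception. It matters here because fhSPECT follows 15 minutes of drainage and SPECT/CT may come up to 24 hours later, so some non-matching nodes may reflect later drainage.
4. Have question 3 answered per node where a patient has several contralateral nodes.
5. In Validating image protocol, state that agreement requires co-localisation when both scans are positive.
6. Report side-only detection as a descriptive figure.

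The cost is a few sentences of wording and a small change to the form. Neck levels are already recorded, but question 3 is asked once per case, so patients with several nodes need additional entries, including a re-read for those already assessed. Reported sensitivity and agreement may be somewhat lower.

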#### Justification for trial and comparators

The mechanism of reliability of lymphatic mapping to sentinel nodes was first described in 2007.^17^ Functional lymphatic imaging studies were undertaken in tumour and control footpads of mice. Tracer showed in the sentinel node within 2 min of injection compared with 30 min for the control. Histologically, sentinel nodes had c-Myc oncogene overexpression stimulating VEGF-C and VEGF-D to induce lymphangiogenesis in the node, causing a 23-fold increase in lymphatic tracer drainage. Lymphatic mapping reveals an active premetastatic process directing lymphatic flow to specific nodes. Human studies in oral cancer showed patients injected and imaged on two separate occasions a week apart had drainage to identical nodes.^18^

The LOOC trial will allow a choice of lymphatic mapping radiotracer, 99mTc-human albumin colloidal particles or 99mTc-Lymphoseek. 99mTc-human albumin colloidal particles are standard radiotracers, which accumulate within LN. These have a large body of evidence supporting efficacy in the mapping of sentinel nodes from oral cancer and more recently have been used to map lymphatic drainage in patients with cN0 OPC under general anaesthetic.^19^ In this study, patients were imaged by single photon emission CT (SPECT)/CT 3–6 hours postinjection with a contralateral drainage rate of 20%.

Lymphoseek has additional properties to aid retention in the sentinel node via binding to macrophage CD206 mannose receptor. The advantage of rapidly clearing the injection site while selectively retaining the substance in the sentinel node is crucial in LOOC, where the goal is to image the sentinel nodes in the operating theatre within minutes of injection. Scatter and ‘shine-through effect’ in traditional tracers can impair immediate imaging, but Lymphoseek has not been compared with traditional tracers within the intraoperative setting. Over a longer protocol, Lymphoseek has shown impressive results in reducing the false negative rate for sentinel node biopsy (SNB in oral tumours from 9% to 2.56%. Due to licensing arrangements, Lymphoseek is only intermittently available in Europe; therefore, the LOOC trial pragmatically allows investigators the choice of Lymphoseek or a standard colloid tracer. This protocol allows for ad hoc interim analysis to ensure there is no significant difference in the total number of nodes and contralateral nodes identified by each tracer.

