### Statistical methods

#### Validating image protocol

Patients will be assessed with both imaging procedures (fhSPECT and SPECT/CT), with SPECT/CT being considered the gold standard—to allow assessment of sensitivity and specificity of fhSPECT (including positive predictive value and negative predictive value). The agreement between fhSPECT and SPECT/CT will be recorded as either agree or disagree and will be calculated with an exact 95% CI. Two independent assessors will consider each pair of scans. We will investigate the agreement between these assessors and quantify the corresponding intra-class correlation.

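### The rule for scoring the scans contradicts the stated SPECT/CT reference standard; if followed, it leaves fhSPECT with no possible false positive

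*Protocol article*

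**What the plan says.** Three parts of the protocol article define truth for the imaging phase.

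- **Statistical methods, Validating image protocol.** Patients have both scans, "with SPECT/CT being considered the gold standard—to allow assessment of sensitivity and specificity of fhSPECT", "including positive predictive value and negative predictive value".
- **Outcomes, Imaging phase.** For the secondary outcome, accuracy: "Number of contralateral nodes on SPECT/CT used as denominator in calculating sensitivity of fhSPECT by independently verified images". The Abstract says the same. For the primary outcome, the drainage rate, both scans are combined: "Sum of non-duplicated contralateral hotspots taken as the true contralateral drainage rate". The minimum of 20 of 75 patients with contralateral drainage follows directly.
- **Imaging phase outcome measure data collection.** "If contralateral nodes are shown in SPECT/CT but not on fhSPECT, this will be recorded as a false negative result", with an exception for second echelon nodes, "for fhSPECT and vice versa". Then: "Contralateral drainage on either modality will be recorded as a true positive result". The next sentence sets the sensitivity target above 94% compared with SPECT/CT.

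The Abstract ties sensitivity below 94% to a secondary imaging protocol. The Surgical phase section under Planned interventions says that imaging-phase outcomes inform which of two imaging routes is used.

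**The concern.** The either-scan sentence fits the primary outcome, where the union of the two scans is the declared truth. It stands, however, among the accuracy scoring rules, between the definition of a false negative and the 94% criterion. There it makes the test under evaluation part of its own reference standard. A contralateral hotspot seen only on fhSPECT becomes a true positive and, by the reversed half of the preceding sentence, a SPECT/CT miss. No outcome is left that counts against fhSPECT for showing drainage that the gold standard does not show.

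Two of the four planned accuracy measures would then carry no information, and the sensitivity numerator could include cases outside the SPECT/CT denominator. An analyst following the data-collection section and one following the statistical methods could report different results from the same scans.

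**Working it through.** **The plan's own figures.** The Sample size section expects 96% agreement in 75 patients, an exact 95% CI about 10% wide, and 80% power to show agreement above 88% (one-sided 5%). For 72/75 the Clopper-Pearson interval is 88.8% to 99.2%, width 10.4%. Declaring success at 71/75 or more gives a type I error of 0.0449 and power of 81.9%. Both figures reproduce. They concern agreement, so the choice of reference does not affect them.

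**Notation, per patient.** a = both scans positive, b = fhSPECT only, c = SPECT/CT only, d = neither. The protocol gives no expected discordance by direction, so all counts below are assumptions. The plan defines sensitivity over nodes; patients are used here because specificity needs a count of negatives.

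| Measure | SPECT/CT as reference | Either-scan rule |
|---|---|---|
| Sensitivity | a/(a+c) | (a+b)/(a+b+c) |
| Specificity | d/(b+d) | d/d |
| PPV | a/(a+b) | (a+b)/(a+b) |
| NPV | d/(c+d) | d/(c+d) |

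**Step 1: specificity and PPV.** Under the either-scan rule b moves to the true positives and the false-positive count is zero. Both measures are 100% for any b, provided the cells are not empty. This needs no assumed counts.

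**Step 2: double classification.** A SPECT/CT-only case is a false negative for fhSPECT by one sentence and a true positive by the next, so read literally c is counted in both cells.

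**Step 3: an illustrative table.** a/b/c/d = 15/4/1/55:

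- SPECT/CT reference: sensitivity 15/16 = 93.8%, specificity 55/59 = 93.2%, PPV 15/19 = 78.9%.
- Either-scan rule: sensitivity 19/20 = 95.0%, specificity 55/55 = 100%, PPV 19/19 = 100%.
- NPV is 55/56 = 98.2% under both.

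Sensitivity falls on opposite sides of 94%. Agreement is 70/75 = 93.3%, below the planned 96%.

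**Step 4: how often the threshold result changes.**

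- With 15 patients positive on either scan, no table changes it.
- With 20, c must be 1 (c = 2 gives 18/20 = 90%), and then a/(a+1) ≤ 0.94 requires a ≤ 15, so b ≥ 4.
- At exactly 72/75 agreement, b + c = 3. For c = 1, b = 2, the two conditions a/(a+1) ≤ 0.94 and (a+2)/(a+3) > 0.94 leave a = 14 or 15. For c = 2, b = 1, they leave a = 31. For c = 0 or b = 0 there is no change. The first two tables have 17 and 18 patients positive on either scan, below 20 of 75. The third has 34/75 = 45%, with sensitivity 31/33 = 93.9% against 32/34 = 94.1%.

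**Step 5: mixing the sections.** True positives from the data-collection section over the SPECT/CT denominator give (a+b)/(a+c). For 18/1/2/54 (agreement 96%) this is 19/20 = 95.0% instead of 18/20 = 90.0%. For 15/4/1/55 it is 19/16 = 118.8%, which is not a proportion and shows that the two rules cannot be combined.

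**The case against.** The case for leaving the text alone is substantial.

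- The reference for sensitivity is already fixed. The Abstract and the Outcomes section both use SPECT/CT nodes as denominator, the data-collection section itself ends by comparing with SPECT/CT, and no section gives a union denominator for sensitivity.
- The data-collection section covers both imaging outcomes, so the either-scan sentence may have been meant for the primary outcome. The reversed half of the preceding sentence might likewise have been meant to make an fhSPECT-only finding a false positive.
- The form records each scan and their co-localisation separately, so the patient-level table against SPECT/CT stays recoverable.
- Specificity and PPV drive no decision rule.

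Most of this stands and limits the size of the point. It does not remove the contradiction: the sentence is not restricted to the primary outcome, it directly precedes the accuracy target, and with it in force an fhSPECT-only finding cannot be a false positive.

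Three stronger readings are tempting and not supported. A reader might infer that specificity and PPV will be 100% in any event; if the Statistical methods section is applied strictly, they vary freely. A reader might infer that using the union for the 20 of 75 rule is an error; the Outcomes section states the union and the minimum together, and the Background reports a higher false negative rate for SPECT/CT than for fhSPECT in oral cancer (15.8% against 5.3%), so the choice is open and defensible. A reader might infer that early artefacts will be counted as drainage; the protocol says only "Scatter and ‘shine-through effect’ in traditional tracers can impair immediate imaging", not that they create false contralateral hotspots.

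**Conclusion.** The point holds as a contradiction between a stated scoring rule and the stated reference standard. Its firm consequence is conditional: if the scoring rule fills the two-by-two table, fhSPECT specificity and PPV equal 100% by definition and tell the reader nothing. That rests only on non-empty cells.

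The effect on the 94% criterion is weaker. A changed result is possible, as 15/4/1/55 shows, but it needs particular counts. At the planned 96% agreement, comparing the SPECT/CT reference with the either-scan rule, it arises only where fewer than 20 patients drain, so that the surgical phase would not proceed on either count, or at about 45% drainage, well above the 20% to 30% in the Sample size section. It should not be presented as the expected outcome. The planned power and precision for agreement are unaffected.

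**What to change.** Reword the data-collection section:

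1. Limit the either-scan sentence to the primary outcome, the contralateral drainage rate.
2. For the accuracy analysis, use SPECT/CT alone as reference: fhSPECT-only is a false positive and SPECT/CT-only is a false negative, keeping the second-echelon exception.
3. State that the 94% criterion is computed over SPECT/CT-positive nodes only, in line with the Outcomes section.

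The union may remain the primary outcome and the basis of the 20 of 75 rule. A drainage rate by SPECT/CT alone beside it is an optional sensitivity analysis.

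The cost is a few sentences. The form already records each scan separately, so no new data are needed. The drawback is that fhSPECT specificity and PPV may look less favourable. Recruitment is under way, so the change should be made before the imaging-phase results are examined; otherwise the reference could be chosen with the answer known.
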